### Trial status

Recruitment of participants to the study will start from 7 April 2025. It is expected that recruitment will finish by 1 October 2025 and that data collection will be finished by the end of January 2026.

## Discussion

This paper details the design of a clinical acceptability and feasibility study of a strengths and needs assessment for autistic adults. The study aims to evaluate the acceptability of implementing this assessment in post-diagnostic care and the acceptability and feasibility of the trial design in preparation for a future large-scale RCT.

The ICF CoreSets for Autism Strengths and Needs Assessment and associated summary report has the potential to be used by autistic adults to better understand where they would benefit from support and to self-manage this support in a range of contexts. With its inclusion of strengths, it also has the potential of moving away from a deficit-oriented framework to a more person-centred approach.

Previous research with autistic adults has reported that existing post-diagnostic support does not meet their needs and that a personalised support plan is something which autistic people would value.^6 17^ The importance of early support for autistic adults has also been highlighted. Clinicians report a lack of standardised planning procedures for post-diagnostic support and having to spend time and resources on producing individual provision. Therefore, providing a standardised method of planning post-diagnostic support has the potential to benefit autistic adults and clinicians.

Before the development of the ICF CoreSet for Autism, there was a lack of comprehensive assessments which captured the lived experience of autistic people. Previous tools were often narrow, deficit-focused or not specific to autism.^27 48^ Alternative approaches to measuring functioning could include using QoL measures such as WHOQOL-BREF^49^ or WHOQOL-DIS,^50^ or more autism-specific needs assessments (eg, the Social Responsiveness Scale).^51^ However, these approaches lack the comprehensive and standardised framework of the WHO’s ICF classifications of functioning and should be seen as additional approaches rather than as something which could replace the ICF framework. Using the ICF framework allows insights to be used by autistic people in a range of settings (eg, education, health, employment). Other approaches also tend to focus on the individual rather than on highlighting how the environment can impact on daily functioning and stress either strengths or needs without including the interaction between the two.

This study builds on previous piloting of the ICF CoreSets for Autism Strengths and Needs assessment which suggests that it is acceptable and usable both for supported and self-completion,^28 31^ which describes the psychometric properties of the assessment.^28^ This study is looking at whether the period immediately following diagnosis is an acceptable and feasible time to offer this assessment. It is also the first time the summary report has been trialled in the UK.

A strength of the study is its co-design with autistic adults. A steering group will oversee the study at all stages from design to dissemination of results. All study materials, including participant information sheets and interview schedules, will be co-designed with the steering group and the autistic PPI who is a co-investigator in the project. This will positively impact the validity of the study and ensure that it is acceptable to the autistic community.

There are some issues which could arise during this pilot trial. First, the ICF CoreSets for Autism Strengths and Needs Assessment is a long assessment (265 items). This could be a burden to participants, especially as it is presented at a potentially overwhelming time (immediately following diagnosis). In collaboration with our steering group of autistic adults, we have put procedures in place to reduce the burden of completing the assessment. First, participants are under no obligation to take part in the study and only contact the research team if they wish to participate. The information sheets highlight the length of the assessment and include previous completion times to set clear expectations about what we are asking participants to do. Participants will be given 2 weeks to complete the assessment and can do it in as many sittings as they like. When participants are sent a link to the assessment, they will be told that the researcher is available to help with anything which is unclear. Participants can ask others (eg, family, friend, supporter) to help them to complete the assessment if they wish and they are free to leave the study at any time. Any feedback which we receive, via email, about the comprehensibility and format of the assessment will feed into the ongoing development of the assessment. It is also important to note that previous trials have demonstrated a high rate of completion (eg, 91% for self-completion)^31^ and good levels of acceptability and usability across a range of studies.^28 31^

It is also possible that there could be higher attrition in the treatment as usual group as they will not be offered the chance to complete the ICF CoreSets for Autism Strengths and Needs Assessment. Higher levels of attrition in control arms of RCTs have been reported.^52^ To mitigate this risk, all the participant information sheets emphasise the importance of having a control group. Both the assessment and treatment as usual groups will also receive the same payment for taking part in the study. Whether being placed in the treatment as usual group is a disincentive for participation will be explored further in the interviews with a subset of participants as part of the trial process evaluation.

As participants self-select into the study, this may lead to some selection bias due to particular groups being less likely to enrol. To explore this, we will record demographic information about age, gender and ethnicity. As well as using this data to balance the assessment and treatment as usual groups, we will also use it to demonstrate the representativeness of our sample. As this is a feasibility trial, this will be helpful in planning a future trial and may suggest groups who might require more support to take part. As clinical sites record the numbers of leaflets they distribute, it will be possible to report recruitment rates (eligibility/number recruited). To address digital exclusion, we will offer participants who are not able to complete the study on a computer or phone the option of completing measures via post or supported by a researcher in their clinical setting.

The development and implementation of a standardised strengths and needs assessment for autistic adults are in line with the priorities of the NHS long-term plan^11^ and the Department of Health and Social Care’s (2021–2026) strategy,^10^ to improve post-diagnostic support and reduce health inequalities for autistic people. This pilot trial represents a first stage in evaluating these trial procedures in preparation for a larger scale RCT. The three sites included in this pilot have different post-diagnostic support pathways, are in different geographic locations and catchment areas and have different numbers of people coming through their services. This increases the generalisability of the results and the usefulness of the trial process evaluation. A larger scale RCT will then be needed to evaluate whether this assessment could offer a standardised approach to evaluating individual support needs in NHS diagnostic centres.

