The study will also evaluate the acceptability and feasibility of the trial design in preparation for a future definitive randomised control trial (RCT). The UK’s Medical Research Council’s framework for evaluating complex interventions^34^ highlights the importance of piloting prior to larger efficacy trials being carried out. This identifies potential problems which could lead to underpowering in larger trials and provides estimates for trial sample sizes. Acceptability will be evaluated in interviews with participants and focus groups with clinicians. The feasibility of the proposed recruitment, randomisation and data collection methods will be evaluated against a list of progression criteria before planning for a future trial.

Specifically, the research questions are

RQ1a: Are the proposed recruitment, randomisation and data collection methods acceptable and feasible for use within NHS adult autism diagnostic services?

RQ1b: Is the ICF CoreSets for Autism Strengths and Needs Assessment acceptable for use by autistic adults on receipt of an autism diagnosis?

RQ1c: What are the potential benefits or harms of completion of the ICF CoreSets for Autism Strengths and Needs Assessment?

The secondary aim is to gain a thorough understanding of the characteristics and mental health status of the populations receiving autism diagnoses in these clinical settings. We will use mental health and quality of life (QoL) outcome measures to answer the secondary research question:

RQ2: What are the demographics and current mental health status of adults being diagnosed in NHS services?

Mental health measures will also be used to monitor for adverse events arising from study participation. They will also provide preliminary data on whether the strengths and needs assessment improves well-being outcomes and how feasible it is to use these measures to measure efficacy in a larger trial.

The study will be reported according to Consolidated Standards of Reporting Trials guidelines for reporting randomised pilot and feasibility trials.^35^ If effective, the ICF CoreSets for Autism Strengths and Needs Assessment have the potential to be implemented in NHS diagnostic services as a standardised approach to providing post-diagnostic support for autistic adults.

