### Study procedures

Service users who receive a diagnosis of autism and meet the other eligibility criteria (18+ years old, no diagnosis of intellectual disability) will be given information about the study (written information leaflet, verbal information) by their diagnosing clinician which includes links to access further information about the study and contact details for the research team at the University of Sheffield. This will be given alongside other standard care information (eg, signposting to resources, information about their service’s post-diagnostic provision) at the appointment where they receive their diagnosis. The full information sheets for the study have been provided in standard and Easy Read/Plain English versions. Participants will have 4 weeks from the date of their diagnosis to decide whether they would like to participate in the study. They will be able to access a form to consent to participate and to provide their contact details via the links provided in the information leaflet.

Participants will be emailed a link to complete a short demographic questionnaire (age, gender, ethnicity, diagnosing service, date of diagnosis). Following this, they will be randomised into either the assessment group (n*=*36) or the treatment as usual group (n*=*36) by the research team at the University of Sheffield. This will be done using a minimisation approach which allows demographic factors to be balanced across groups in ongoing recruitment. This will be done using software developed by researchers at the University of York^36^ and will balance three factors (gender, age, ethnicity) with two levels for each factor (male/female, under/over 40, white/non-white) in each study arm. All participants will continue with the standard care offered by their clinical site during the study. This may include signposting to resources, follow-on appointments and psychoeducational input. It is not possible to blind participants to group allocation. However, clinicians will not be informed about individual participation or group allocation.

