### Data analysis

Descriptive data for all demographic variables will be presented by trial arm to provide an overview of the cohort of participants recruited to the study, to evaluate the group allocation methods and to demonstrate the representativeness of the sample. Means and SD will be reported for the QoL and mental health measures. These will be compared with clinical cut-offs to indicate levels of well-being in the sample.

Eligibility rate, recruitment rate, completion rates and times for the strengths and needs assessment and the outcome measures will be reported descriptively. Sample medians will be used as an estimate of average completion times. CIs will indicate completion time variance.

Participants will be given 2 weeks to complete the strengths and needs assessment and the QoL/mental health measure questionnaire. After 1 week, they will be sent a reminder and offered support if they need it. After 2 weeks, they will be considered ‘lost to contact’ and will be sent a debrief form with links to support organisations. The number of participants ‘lost to contact’ or withdrawn will be recorded as part of the trial evaluation. If participants start but do not complete the strengths and needs assessment, we will record the time they spend on the assessment and the proportion completed. Any data previously given by participants who are ‘lost to contact’ or withdraw will still be analysed unless participants ask us to withdraw their data.

Preliminary effectiveness of the strengths and needs assessment will be assessed using mixed model analyses of covariance. These analyses will determine whether QoL (assessed using EQ-5D-5L and ReQoL-10) and mental health (assessed using PHQ-9 and GAD-7) changes between baseline and 3 months post-intervention are affected by allocation to the assessment/TAU group. The analyses will statistically control for demographic variables and clinical site. Effect size will be reported using partial eta-squared which will inform the sample size calculation for the definitive trial (RCT).

Qualitative data from the interviews and focus groups will be analysed using NVivo.^45^ Questions pertaining to acceptability and feasibility of the trial procedure will be analysed using thematic content analysis.^46^ Experience of post-diagnostic service provision more generally will be analysed using a reflexive thematic analysis approach.^47^

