### Reliability and validity

Providing a study identifier on each information leaflet means that only one participant can use it to register onto the study and will ensure that participants are coming from one of the participating services. No recruitment will be done via other methods.

Using a minimisation method for randomisation will reduce the risk of selection and allocation bias. It will also ensure that we balance demographic factors across the two groups. It is not possible to blind participants to which group they have been assigned. However, clinicians will not be informed about whether participants have consented to participate, or which group they were allocated to. This is done to maintain the treatment as usual care of all participants. The feasibility of clinician blinding will be assessed as part of the study evaluation.

More than one researcher will code qualitative interview and focus group data, and inter-rater reliability will be measured. Coding frames will be discussed and agreed by wider members of the research team following guidance from qualitative data analysis methodology.^47^

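### The recruitment rate is printed as its own reciprocal, and representativeness is to be shown from enrolled participants' demographics with no comparator named

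*Protocol article*

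**What the plan says.** On the rate, the Discussion says: "As clinical sites record the numbers of leaflets they distribute, it will be possible to report recruitment rates (eligibility/number recruited"). Data analysis lists the recruitment rate among quantities to be reported descriptively but gives no formula, so the Discussion holds the only definition in the article.

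On who is counted, Study procedures says that newly diagnosed service users who meet the eligibility criteria "will be given information about the study (written information leaflet, verbal information) by their diagnosing clinician". Reliability and validity adds: "Providing a study identifier on each information leaflet means that only one participant can use it to register onto the study". Primary outcome measures includes service users' eligibility rates among the procedural data collected from sites, and Data analysis reports an eligibility rate separately from the recruitment rate.

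On selection, the Discussion accepts that self-selection may leave some groups under-enrolled. Its response is to record age, gender and ethnicity, and of these data it says "we will also use it to demonstrate the representativeness of our sample". Data analysis gives the descriptive tables a matching purpose: "to demonstrate the representativeness of the sample". Under Study procedures these variables come from a questionnaire emailed to people who have consented and left contact details. Secondary outcome measures confines the demographic outcome to the recruited adults.

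RQ2 in the Introduction is wider: "What are the demographics and current mental health status of adults being diagnosed in NHS services"?

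**The concern.** Two things look wrong, and they differ in weight.

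The first is the direction of the ratio. A recruitment rate has the recruited in the numerator. The printed form is at least 1 whenever recruits do not outnumber those eligible, and it rises as recruitment gets worse.

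The second is the evidence for representativeness. A sample is representative of something, and the article does not say of what. Primary, Secondary outcome measures, Data analysis and the Discussion all mention representativeness, and none names leaflet recipients, eligible adults, the service caseload or an outside source as the comparator. Demographics of participants alone cannot reveal which groups stayed away.

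Recruitment rates and representativeness sit under the primary outcome measures, and the Introduction says that recruitment feasibility will be judged against progression criteria. The Discussion also hopes to identify groups who may need more support to take part, which requires a denominator for each group. RQ2 asks about everyone being diagnosed but would be answered from volunteers.

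**Working it through.** **Inputs from the article.** Target recruited: 3 services × 24 = 72, and 2 arms × 36 = 72; the two statements agree. No leaflet count, eligible count or demographic share is given, so the recruitment rate itself cannot be reproduced. Every such figure below is an illustrative assumption.

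**Step 1: direction of the ratio.** Let L be the number of leaflets given out. As printed the quantity is L/72; the rate is 72/L (Wilson 95% CI).

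| Assumed L | As printed, L/72 | Rate, 72/L | 95% CI |
|---|---|---|---|
| 90 | 1.25 | 80% | 71–87% |
| 144 | 2.00 | 50% | 42–58% |
| 200 | 2.78 | 36% | 30–43% |
| 360 | 5.00 | 20% | 16–24% |

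Both counts are collected, so the correction needs no new data.

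**Step 2: leaflets against eligible adults.** If clinicians reach a fraction r of eligible adults, the number eligible is L/r and recruited/eligible is 72r/L. For L = 200:

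- r = 100%: 200 eligible, 72/200 = 36%
- r = 80%: 250 eligible, 72/250 = 29%
- r = 50%: 400 eligible, 72/400 = 18%

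The leaflet count alone cannot separate these cases. The site eligibility data can, provided they are kept as counts. The denominator matters because Participants ends recruitment at a service once 24 have been recruited. Where that target is met the numerator is fixed, and the denominator and the time taken carry the feasibility information.

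**Step 3: representativeness.** Suppose 14 of 72 participants are non-white (19%; Wilson 95% CI 12–30%), leaving 58 white. If a share s of those invited is non-white, the ratio of non-white to white uptake is

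(14 / sL) ÷ (58 / (1 − s)L) = (14/58) × (1 − s)/s.

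L cancels, so the result does not depend on the number of leaflets.

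| Assumed s | Uptake ratio, non-white : white |
|---|---|
| 10% | 2.17 |
| 20% | 0.97 |
| 30% | 0.56 |
| 40% | 0.36 |

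The same participant data fit more than double the uptake and little more than a third of it. What decides between them is s, and no section says how s will be obtained.

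**The case against.** The case on the other side has real force in several places.

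- **The bracket is a slip in a Discussion aside.** The slash could be a loose label for two counts. A ratio is the more natural reading after the words recruitment rates, but the slip changes no data and no design step. This stands: taken alone, it is a wording correction.
- **Reach.** A reader might infer that basing the rate on leaflets makes reach impossible to show, because eligible adults who were never approached drop out of the count. The document does not support that. By procedure, leaflets go to service users who meet the criteria, so recruited/leaflets is a valid uptake among those invited. Site eligibility rates are also collected and reported, and recruited/eligible can be derived from the underlying counts. The 50% case in the working departs from the stated procedure and only illustrates sensitivity.
- **RQ2 is already narrowed.** Secondary outcome measures defines the outcome in recruited adults, and the Discussion acknowledges self-selection. This stands in part: the outcome is limited, but the research question is not, and the representativeness claim is what would bridge the two.
- **The article is condensed.** The full protocol may name a comparator. That is possible, and silence alone would not be a finding. But the article is not silent: it states a method and says that the method will demonstrate representativeness, and that method cannot do so.

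A reader might also infer that the inverted rate would mis-set the number of sites in the definitive trial. Nothing in the article makes that link.

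**Conclusion.** The point holds in two parts. The printed recruitment rate is the reciprocal of the quantity intended; this is an error of wording that is corrected from counts already collected. The more substantial defect is that selection bias and representativeness are to be assessed from consenters' demographics with no comparator named. Under the illustrative 14 of 72, the data are compatible with uptake ratios from 2.17 to 0.36 as the non-white share of those invited goes from 10% to 40%. The stated method therefore cannot support the representativeness outcome, or an RQ2 conclusion about all adults diagnosed.

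The size of any actual selection is unknown. The direction of the printed ratio and the need for a comparator do not depend on the assumed counts. The conclusion is limited to what the article states and would fall away in its second part if the full protocol names a comparator.

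**What to change.** 1. Define the recruitment rate as number recruited/number eligible, with number recruited/leaflets given alongside, each by site. Ask sites to supply the eligibility data they already provide as counts rather than only as rates.
2. Obtain from each site one aggregate, anonymous table of eligible adults diagnosed while that site was recruiting, by age band, gender and ethnicity, at categories that match the participant questionnaire. Name it as the comparator in Data analysis and compare participants with it.
3. If a site cannot supply the table, state that the demographics describe the sample, drop the claim to demonstrate representativeness, and limit the RQ2 conclusion to adults who enrolled.

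The cost is one corrected formula, a little administration at each of three sites and possibly a less favourable rate. The table can be compiled at the end of recruitment and changes nothing for participants.
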